## **7.4. Pharmacokinetics**

### **7.4.1. Blood Sample Collection**

Blood samples for pharmacokinetic analysis of UMEC and VI will be collected at the time points indicated in Section 4.6, Time and Events Table. The actual date and time of each blood sample collection will be recorded. The timing of PK samples may be altered and/or PK samples may be obtained at additional time points to ensure thorough PK monitoring.

Details of PK blood sample collection (including volume to be collected), processing, storage and shipping procedures are provided in the Study Procedures Manual (SPM).

### **7.4.2. Sample Analysis**

Concentrations of UMEC and VI will be determined in plasma using the currently approved analytical methodology.

## **8. LIFESTYLE AND/OR DIETARY RESTRICTIONS**

### **8.1. Contraception Requirements**

#### **8.1.1. Female Subjects**

Female subjects of childbearing potential must not become pregnant and so must be sexually inactive by abstinence or use contraceptive methods with a failure rate of < 1%.

**Abstinence**

Sexual inactivity by abstinence must be consistent with the preferred and usual lifestyle of the subject. Periodic abstinence (e.g. calendar, ovulation, symptothermal, post-ovulation methods) and withdrawal are not acceptable methods of contraception.

**Contraceptive Methods with a Failure Rate of < 1%**

- Oral contraceptive, either combined or progestogen alone
- Injectable progestogen
- Implants of levonorgestrel
- Estrogenic vaginal ring
- Percutaneous contraceptive patches
- Intrauterine device (IUD) or intrauterine system (IUS) that meets the <1% failure rate as stated in the product label
- Male partner sterilization (vasectomy with documentation of azoospermia) prior to the female subject's entry into the study, and this male is the sole partner for that subject. For this definition, “documented” refers to the outcome of the investigator's/designee's medical examination of the subject or review of the subject's medical history for study eligibility, as obtained via a verbal interview with the subject or from the subject's medical records.
- Double barrier method: condom and occlusive cap (diaphragm or cervical/vault caps) plus spermicidal agent (foam/gel/film/cream/suppository)

**These allowed methods of contraception are only effective when used consistently, correctly and in accordance with the product label. The investigator is responsible for ensuring subjects understand how to properly use these methods of contraception.**

**8.1.2. Male Subjects**

Male subjects with female partners of child-bearing potential must use one of the following contraceptive methods after the first dose of study treatment and until the follow-up contact:

- Condom plus partner use of a highly effective contraceptive such as occlusive cap (diaphragm or cervical/vault cap) plus spermicidal agent (foam/gel/film/cream/suppository), oral contraceptive, injectable progesterone, implant of etonogestrel or levonorgestrel, estrogenic vaginal ring, percutaneous contraceptive patches, or intrauterine device. **OR**
- Abstinence, defined as sexual inactivity consistent with the preferred and usual lifestyle of the subject. Periodic abstinence (e.g. calendar, ovulation, symptothermal, post-ovulation methods) and withdrawal are not acceptable methods of contraception

## 8.2. Meals and Dietary Restrictions

- Subjects will be required to follow the fasting restrictions described below:

| Treatment period | Morning                           |
|------------------|-----------------------------------|
| Day 1, 10        | Fast: 4hr predose – 4hr post dose |
| Day 6,7,8,9      | Fast: 2hr predose – 1hr post dose |

- Water will be allowed freely, except for 1hour either side of dosing on all dosing occasions.
- Subjects must refrain from grapefruit or grapefruit juice containing products from 7 days pre-dose (Day 1) of the first treatment period until collection of the final PK blood sample. Subsequent meals and snacks will be standardized for all subjects during their in-site period.

## 8.3. Caffeine, Alcohol, and Tobacco

- During each dosing session, subjects will abstain from ingesting caffeine- or xanthine-containing products (e.g. coffee, tea, cola drinks, and chocolate) for 24 hours prior to the start of dosing until collection of the final pharmacokinetic and or pharmacodynamic sample during each session.
- During each dosing session, subjects will abstain from alcohol for 24 hours prior to the start of dosing until collection of the final pharmacokinetic and or pharmacodynamic sample during each session.
- Use of tobacco products is not allowed from screening until after the final follow-up visit.

## 8.4. Activity

Subjects will abstain from strenuous exercise for 48 hours prior to each blood collection for clinical laboratory tests. Subjects may participate in light recreational activities during studies (e.g., watch television, read). Strong activities and long time bed rest should be avoided.

## 9. CONCOMITANT MEDICATIONS AND NON-DRUG THERAPIES

### 9.1. Permitted Medications

Subjects may take simple analgesics, such as paracetamol/acetaminophen, aspirin, ibuprofen, and et al, following the prescription of professional physician.

## **9.2. Prohibited Medications**

Other than simple analgesics, such as paracetamol/acetaminophen, aspirin, ibuprofen, and et al , subjects must abstain from taking prescription or non-prescription drugs (including vitamins and dietary or herbal supplements), within 7 days (or 14 days if the drug is a potential enzyme inducer) or 5 half-lives (whichever is longer) prior to the first dose of study medication until completion of the follow-up visit, unless in the opinion of the Investigator and sponsor the medication will not interfere with the study.

The Investigator (or designated study physician) must be informed as soon as possible about any medication taken from the time of screening until the end of the clinical phase of the study (follow-up visit).

All concomitant medications taken during the study will be recorded in the CRF. The minimum requirement is that drug name and the dates of administration are to be recorded.

## **9.3. Non-Drug Therapies**

The Investigator (or designated study physician) must be informed as soon as possible about any non-drug therapies from the time of screening until the end of the clinical phase of the study (follow-up visit).

# **10. COMPLETION OR EARLY WITHDRAWAL OF SUBJECTS**

## **10.1. Subject Completion**

A completed subject is one who has completed all phases of the study including the follow-up visit.

The end of the study is defined as the last subject's last visit.

## **10.2. Subject Withdrawal Criteria**

Refer to Section 4.5 for dose adjustment/stopping criteria based on safety/PK/PD criteria.

A subject may withdraw from study treatment at any time at his/her own request, or may be withdrawn at any time at the discretion of the investigator for safety, behavioral or administrative reasons.

## **10.3. Subject Withdrawal Procedures**

### **10.3.1. Subject Withdrawal from Study**

For subjects withdrawn from the investigational product, follow-up procedures should be performed. Relevant pages of the CRF should be completed by the investigator

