**Table 1 Regimens of the study**

| Regimens | Treatments (inhaled once daily for 10 days) |              |
|----------|---------------------------------------------|--------------|
|          | NDPI Strip 1                                | NDPI Strip 2 |
| A        | UMEC 62.5µg                                 | VI 25µg      |
| B        | UMEC 125µg                                  | VI 25µg      |
| C        | UMEC 62.5µg                                 | N/A          |
| D        | UMEC 125µg                                  | N/A          |
| E        | VI 25µg                                     | N/A          |

N/A=Not Applicable

The order in which these treatments are administered will be in accordance with the randomisation schedule, and there will be a minimum washout period of 7-14 days between periods.

Each subject will be admitted to the unit in the evening prior to Day 1 and remain resident until all assessments completed on D12. All subjects will be scheduled for a follow up visit, 7-10 days after their final dose.

The overall maximum duration (screening to follow-up) for participating subjects will be about 13 weeks.

Protocol waivers or exemptions are not allowed. Therefore, adherence to the study design requirements, including those specified in the Time and Events Table, are essential

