| Serology (HIV, Hep B & C)                   | X              |                    |       |       |       |       |       |       |       |       |       |        |                |                |                           |
| Drugs of abuse screen                       | X              |                    |       |       |       |       |       |       |       |       |       |        |                |                |                           |
| Alcohol breath test and urine cotinine test | X              | X                  |       |       |       |       |       |       |       |       |       |        |                |                |                           |
| Laboratory safety tests         | X              | X      |       |       |       |       |       |       |       |       |       |        | X              |                | X             |
| Vital signs (HR and BP)                     | X  | X                  | X     | X     | X     | X     | X     | X     | X     | X     | X     | X      | X              | X              | X                         |
| 12-lead ECG                                 | X  |                    | X     |       |       |       |       |       |       |       |       | X      | X              | X              | X                         |
| Urine pregnancy test                        | X              | X      |       |       |       |       |       |       |       |       |       |        | X  |                |                           |
| Review entry criteria                       | X              | X                  |       |       |       |       |       |       |       |       |       |        |                |                |                           |
| Randomization                               |                | X     |       |       |       |       |       |       |       |       |       |        |                |                |                           |
| Dosing (AM)                                 |                |                    | X     | X     | X     | X     | X     | X     | X     | X     | X     | X      |                |                |                           |

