| Procedure                                              | Screening | day in each period |       |       |       |       |       |                 |                 |                 |                 |        |        |        | Follow-Up |
|--------------------------------------------------------|-----------|--------------------|-------|-------|-------|-------|-------|-----------------|-----------------|-----------------|-----------------|--------|--------|--------|-----------|
|                                                        |           | Day -1             | Day 1 | Day 2 | Day 3 | Day 4 | Day 5 | Day 6           | Day 7           | Day 8           | Day 9           | Day 10 | Day 11 | Day 12 |           |
| Blood PK sampling                                      |           |                    | X     |       |       |       |       | X  | X  | X  | X  | X      | X      | X      |           |
| Unit visit                                             | X         |                    |       |       |       |       |       |                 |                 |                 |                 |        |        |        | X         |
| SAE/AE/concurrent medication questioning  | X         |                    |       |       |       |       |       |                 |                 |                 |                 |        |        |        |           |

1. On day -1 subjects will attend the unit and will be resident until all assessments completed on day12.
2. If a chest X-ray or CT scan is not available within 6 months prior to screening.
3. Physical examination means complete one.
4. Brief physical examination only.
5. Clinical chemistry, haematology & urinalysis.
6. These assessments are taken Day -1 in treatment period 2 and 3.
7. Abnormal lab safety findings post-dosing should be followed up until the tests are normal, stable, no causal relationship with investigational product judged by investigators, or lost contact.
8. Three measurements are to be taken.
9. The test will be taken on Day 11 in the last treatment period.
10. Only on Day-1 in the first treatment period.
11. Blood PK sample will be collected only pre-dosing.

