**7. STUDY ASSESSMENTS AND PROCEDURES**

This section lists the parameters of each planned study assessment. The exact timing of each assessment is listed in the Time and Events Tables (Section 4.6). Detailed procedures for obtaining each assessment are provided in the Study Procedures Manual (SPM).

Whenever vital signs, 12-lead ECGs and blood draws are scheduled for the same nominal time, the assessments should occur in the following order: 12-lead ECG, vital signs, blood draws.

Prior to being enrolled in the study and any study procedures being performed, subjects must sign the informed consent.

Each subject will undergo screening procedures within 21 days of the administration of their first dose of study medication and will have a follow up visit between 7 to 10 days inclusive post their last dose. See Section 4.6. for assessments performed at the screening and follow-up visits.

The timing and number of planned study assessments including safety or pharmacokinetic assessments may be altered during the course of the study based on newly available data (e.g. to obtain data closer to the time of peak plasma concentrations) to ensure appropriate monitoring. The change in timing or addition of time points for any planned study assessments must be approved and documented by GSK, but this will not constitute a protocol amendment. The IRB/IEC will be informed of any safety issues that require alteration of the safety monitoring scheme.

No more than 350 mL of blood will be collected over the duration of the study, including any extra assessments that may be required.

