## **7.2. Safety**

Planned time points for all safety assessments are listed in the Time and Events Table (Section 4.6). Additional time points for safety tests (such as vital signs, physical exams and laboratory safety tests) may be added during the course of the study based on newly available data to ensure appropriate safety monitoring.

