### Other screening tests

|                                                                            |
|----------------------------------------------------------------------------|
| HIV                                                                        |
| Hepatitis B (HBsAg)                                                        |
| Hepatitis C (Hep C antibody )                                              |
| FSH and estradiol (as needed in women of non-child bearing potential only) |
| Alcohol and urine cotinine screen                                          |

Further details regarding these tests can be obtained from the SPM.

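### A woman who stops dosing early generally has no scheduled pregnancy test after her last dose, because Table 2 has none at follow-up and Section 10.3.1 adds none

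*Protocol*

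**What the plan says.** Table 2 (Protocol Section 4.6) has a row headed "Urine pregnancy test", marked at screening, Day -1 and Day 11 only. Footnote 6 limits the Day -1 mark: "These assessments are taken Day -1 in treatment period 2 and 3". Footnote 9 limits the Day 11 mark: "The test will be taken on Day 11 in the last treatment period". The follow-up cell of this row is blank.

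For early stoppers, Section 10.3.1 states: "For subjects withdrawn from the investigational product, follow-up procedures should be performed". It adds completion of the case report form and nothing else. Section 4.1 requires the visit itself: "All subjects will be scheduled for a follow up visit, 7-10 days after their final dose". On the timing of screening, Section 7 says: "Each subject will undergo screening procedures within 21 days of the administration of their first dose of study medication".

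Section 7.3.1 collects pregnancies from the start of dosing to the follow-up visit. Section 7.3.2 sets out reporting to the sponsor and follow-up of the outcome once a pregnancy is known. Women must use contraception, or be abstinent, until follow-up is complete (Sections 5.2.1 and 8.1.1).

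**The concern.** The plan gives each woman who completes a pregnancy test after her last dose. A woman who stops early has also been exposed, but following the schedule as written omits that test for her. If she stops in Period 1, her only scheduled test is the screening one, which may be up to 21 days before her first dose.

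Reporting and outcome follow-up depend on someone knowing of the pregnancy. For an early stopper the follow-up visit is the last planned contact, and pregnancy collection ends there. An exposed early pregnancy that she has not noticed would go unrecorded.

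**Working it through.** **Is a test supplied anywhere else?** The follow-up column of Table 2 holds a brief physical examination, laboratory safety tests, vital signs, an ECG and the unit visit. Footnote 5 defines the laboratory tests as chemistry, haematology and urinalysis, and the urinalysis list in Section 7.2 contains no hCG. The liver follow-up in Section 13 adds no pregnancy test. Section 7.2 also says: "Additional time points for safety tests (such as vital signs, physical exams and laboratory safety tests) may be added". That permits an extra test but does not require one, and it is not tied to withdrawal. No early-termination visit is defined.

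**Who is left without a test after the last dose?**
- Stop during dosing in any period: none scheduled.
- Stop in a washout before the next Day -1 test: none scheduled.
- Leave after a Day -1 test in Period 2 or 3 but before that period's first dose: that test falls after her last dose. This is the one exception.

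**How many women?** The 1:1 sex ratio in Section 5.2.1 gives about 10 of 20. This is an upper figure, since the screening tests in Section 7.2 allow for women not of childbearing potential. The protocol gives no stopping rate. Assuming 10-20%: 10 × 0.10 = 1 and 10 × 0.20 = 2 women.

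**What would a follow-up test add?** Any detection lag applies equally to the last scheduled test and to the follow-up test. The span of newly detectable conceptions is therefore as long as the interval between the two tests. There is no Day 0, the last dose is on Day d, and follow-up is 7-10 days later.

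| Stop | Last scheduled test | Formula (days) | d = 1 | d = 10 |
|---|---|---|---|---|
| Period 1 | Screening, 21 days before Day 1 | 21 + (d − 1) + 7 to 10 | 28-31 | 37-40 |
| Period 2 or 3 | Day -1 | 1 + (d − 1) + 7 to 10 | 8-11 | 17-20 |

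The Period 1 row uses the longest permitted screening interval; later screening shortens it. Of that interval, 21 days precede dosing and apply to all women. The part due to withdrawal is the 0-9 days from first to last dose plus the 7-10 days to follow-up.

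**Expected extra pregnancies found** = women × days/365 × annual rate (both rates assumed):

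| | 8 days | 40 days |
|---|---|---|
| 1 woman, 1% per year | 0.00022 | 0.0011 |
| 1 woman, 10% per year | 0.0022 | 0.011 |
| 2 women, 1% per year | 0.00044 | 0.0022 |
| 2 women, 10% per year | 0.0044 | 0.022 |

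**Which conceptions would it reach?** Assume a lag of 10-14 days from conception to a positive urine test.
- Last dose Day 10, test Day 17-20: conceptions up to Day 3-6 (lag 14) or Day 7-10 (lag 10).
- Last dose Day 1, test Day 8-11: conceptions up to Day -7 to Day -4 (lag 14) or Day -3 to Day 1 (lag 10).

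For a Period 1 stop with last dose on Day 10 and lag 14, 34 of the 37-40 added days fall before Day 1 and 3-6 are dosing days. The gain is mainly for conceptions between screening and early dosing.

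**The case against.** The strongest reply is that the protocol neither errs nor contradicts itself here, and that one more urine test is a matter of preference with almost no yield.

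- **Rate.** Section 8.1.1 requires abstinence or methods with a failure rate below 1%. The 1% line is therefore the one that fits the plan as written, and 10% is only an outer bound. This stands.
- **Residence.** Section 4.1 keeps subjects in the unit from the evening before Day 1 to Day 12. Applying an outpatient rate to days spent in residence overstates the yield. This stands too.
- **A larger gap.** No woman has a Day -1 test in Period 1. Such a test would cover about 20 of the 21 days before dosing and could prevent exposure, where a follow-up test only finds it afterwards. This is true, but that gap is not caused by withdrawal, and closing it would still leave early stoppers untested after dosing.
- **Consistency with completers.** With the same lag, a completer's Day 11 test reaches conceptions only up to Day -4 to Day 1. A withdrawn woman whose last dose was on Day 10 would then be better covered than a completer. That shows how limited either test is, but it does not explain giving early stoppers none.
- **Other routes.** Pregnancies must be collected until follow-up, safety tests may be added, and Section 4.6 refers to the Study Procedures Manual (not available here) for detail. None of these makes the protocol require the test.

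These points reduce the benefit. They do not change what the schedule omits.

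**Conclusion.** The point holds as a minor safety improvement. Under Table 2 and Section 10.3.1, read with the follow-up procedures as the follow-up column of Table 2, a woman who stops before the last period's Day 11 test generally has no pregnancy test after her last dose. Probably 1 to 2 women would be affected, on the assumed 10-20% stopping rate. The expected yield is about 0.0002-0.0011 pregnancies per affected woman at 1% per year, and lower for days spent in residence. Contraception makes such a pregnancy very unlikely, and conception late in dosing would not be reliably detected. The pharmacokinetic results and the sample size are unaffected. The case for the change is its low cost and equal treatment of exposed women.

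**What to change.** In Table 2, mark the urine pregnancy test in the follow-up column, with a footnote limiting it to women of childbearing potential withdrawn before the Day 11 test of the last treatment period. Add one sentence to Section 10.3.1 requiring the same test.

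The cost is one cell, one footnote, one sentence, and one urine test per early-withdrawn woman at a visit Section 4.1 already requires. Two limits remain: the test is lost if she does not return, and after a very early stop it may still be too soon to show a conception during dosing.

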#### **10.4. Treatment after the End of the Study**

Subjects will not receive any additional treatment after completion of the study because only healthy volunteers are eligible for study participation.

#### **10.5. Screen and Baseline Failures**

Data for screen and baseline failures will be collected in source documentation at the site but will not be transmitted to GSK. The reason(s) for excluding these subjects will be documented. The source documentation (including ICF) for all such failures will be made available to the monitor for monitoring.

